## Abstract

**Background:**

Although increasing evidence suggests that repetitive transcranial magnetic stimulation may help improve cognitive impairment after stroke, its clinical efficacy is still limited. This limitation may be due to the fact that the left dorsolateral prefrontal cortex (DLPFC) is only one of several brain areas involved in post-stroke cognitive impairment (PSCI). The aim of the present study is to reveal whether dual-target stimulation is superior to single-target stimulation and usual care in the treatment of PSCI.

**Methods:**

A single-center, single-blind, randomized controlled trial will be conducted, and fifty-seven PSCI patients will be recruited and randomly assigned to one of three groups based on the stimulating site. The primary outcome is cognitive function, measured using the Montreal Cognitive Assessment Beijing Version (MoCA-BJ) and Mini-Mental Status Examination (MMSE). The secondary outcomes are the modified Barthel Index (MBI), Trail-Making Test (TMT), and digital span test (DST). Furthermore, changes in brain activity are assessed using transcranial Doppler sonography (TCD) examination and serum levels of brain-derived neurotrophic factor (BDNF) and vascular endothelial growth factor (VEGF) closely related to nerve and vascular repair after brain injury. All outcomes will be measured at baseline and 4 weeks after treatment.

**Discussion:**

If dual-target rTMS in significant improvements in cognitive function, this method could be considered as a first-line clinical treatment for PSCI. This proposed study has the potential to identify a new, evidence-based intervention that can enhance cognition and independent living in patients with cognitive impairment after stroke.

**Trial registration:**

Chinese Clinical Trial Registry ChiCTR2200066184. It was registered on 26 November 2022.

## Introduction

### Background and rationale {6a}

The Chinese Stroke Report released in 2022 shows that the prevalence rate of stroke in China is 2022.0/100,000, including 1770.7/100,000 for men and 2283.2/100,000 for women [1, 2]. The annual incidence rate is 276.7/100,000, and the mortality is 153.9/100,000. On a global scale, China has become the country with the highest lifelong risk and heaviest disease burden of stroke [3]. Up to one-third of stroke patients will experience post-stroke cognitive impairment [4]. Cognitive impairment is a common and potentially disabling effect of stroke [5]. Post-stroke cognitive impairment (PSCI) is a collective term for differing pathological processes, but regardless of the underlying etiology, stroke survivors and their caregivers consistently rate problems of memory and thinking as their greatest concern [6]. PSCI not only affects the quality of daily life and social adaptability of patients but also has a long-term impact on patients that even exceeds the physical dysfunction itself, seriously affecting the rehabilitation process of patients, and has a high risk of progression to vascular dementia.

Currently, the treatment of PSCI in clinical practice often refers to the treatment of AD, with the principle of improving patient symptoms and delaying disease progression. In addition to medication treatment, rehabilitation training is mainly conducted, but the overall clinical efficacy is unsatisfactory. Rehabilitation training has specific requirements for the patient's limb function. If there is a cognitive impairment, the patient’s ability to understand, execute, and remember will be affected, and they will be unable to manage the training instructions well. Under normal circumstances, the left and right hemispheres of the body are in a balanced state of mutual inhibition. After the stroke, due to the lack of inhibitory effect of the damaged hemisphere on the undamaged hemisphere, it is easy to cause a relative increase in excitability of the intact hemisphere. The inhibitory effect of the damaged hemisphere is exacerbated. Repetitive transcranial magnetic stimulation (rTMS), as a new non-invasive electrophysiological technique, can induce plasticity changes in the central nervous system [7], thereby regulating the excitability of the cerebral hemisphere to change this imbalance after stroke. This study observes the impact of dual-target rTMS on PSCI patients to provide theoretical support for selecting clinical treatment plans.

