### Eligibility criteria {10}

Researchers will conduct eligibility screening based on inclusion and exclusion criteria. All participants should sign an informed consent form after qualification confirmation.

Inclusion criteria:Male or female patients between 18 and 75 years of age;Right-handed;Patients who meet the diagnostic criteria for vascular cognitive impairment reported in the Guidelines from the Vascular Impairment of Cognition Classification Consensus Study [9] and the Chinese vascular cognitive impairment guideline 2019 [10];The patient should have a clear consciousness and stable vital signs. They should also be able to express themselves and understand instructions to a certain extent. At least one limb should be movable without any issues, and the patient must be willing to participate in cognitive assessments and related training actively;The patient had no cognitive impairment before the onset of the disease but had mild to moderate cognitive impairment after the stroke. They had a primary school education level or above, with a score of 9 < MMSE < 27 and a score of 9 < MoCA < 26;No mental illness, no severe aphasia or hearing comprehension disorders; andVoluntary participation and signing the informed consent (signed by the patient or the authorized person).

Exclusion criteria:Cognitive impairment due to primary or secondary neurological disease, such as normal cranial pressure hydrocephalus, frontotemporal dementia, Parkinson’s disease, multiple sclerosis, encephalitis, and delirium;Accompanied with severe mental, intellectual disabilities, or visual and auditory dysfunction, unable to cooperate in completing various functional evaluations;Cognitive impairment due to depression, schizophrenia, bipolar disorder, psychotic disorder, vitamin D deficiency, toxicosis, or else systematic diseases;Drug/alcohol abuse/dependence within the last 3 months of the first recognition of impairment;rTMS treatment contraindications such as epilepsy patients, pregnant or lactating women, or with a metal or electric implanted device (e.g., deep brain stimulator, ventriculoperitoneal shunt, aneurysm clip, pacemaker, cochlear, surgical staples on the scalp);MRI contraindications (such as metal implants or claustrophobia); andParticipating in concurrent pharmacological or nonpharmacologic treatment research.

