#### Localization of stimulation site

The MagPro X100 instrument uses an “8” stimulation coil for transcranial magnetic stimulation in the cortical area, which can collect muscle potential activity. By applying a single pulse stimulation at a higher intensity and moving the coil, the abducts polis MEP > 50 uV can be located and marked as the best stimulation point using a marker. The DLPFC region is targeted for stimulation using the “standard 5 cm” method, which involves translating 5 cm forward from the left M1 region [12].

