### Implementation {16c}

A statistician uses SPSS.25 software to generate random numbers sorted by size. Numbers 1–19 are for the control group, 20–38 are for the single-target stimulation group, and 39–57 are for the double-target stimulation group. Patients are recommended by rehabilitation doctors, therapists, or any other doctor and voluntarily receive rTMS treatment. The doctor randomly assigns 57 patients to any of the three groups according to the results of the random sequence.

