## Statistical methods

### Statistical methods for primary and secondary outcomes {20a}

Statistical analysis will be conducted using SPSS version 25.0 and Microsoft Excel 2016 software.

Measurement data (e.g., MoCA BJ, MMSE, TMT, DST, MBI, BDNF, and VEGF levels in serum, TCD) were statistically described by mean ± standard deviation (*x* ± *s*); count data (such as stroke type, hemiplegic side, and stroke risk factors) were described by frequency (*n*) and percentage (%). The measurement data were first tested for normality, and those not conforming to the normal distribution were expressed by M (P25, P75) and analyzed by Kruskal–Wallis H test; the data conforming to the normal distribution were expressed by *x* ± *s*, one-way analysis of variance was used for comparison between multiple groups, LSD-t-test, and paired *t*-test was used for patients before and after treatment. All test levels were significant at *α* = 0.05 and *P* < 0.05.

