### Methods for additional analyses (e.g., subgroup analyses) {20b}

There are no subgroup analyses planned.

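### Lesion side decides which hemisphere the active arms stimulate, and it is recorded, yet the primary comparison does not adjust for it or for the baseline score

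*Protocol article*

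**What the plan says.** - **Stimulation sites.** Intervention description {11a} fixes the DLPFC target on the left in every group and places the M1 target on the side of the lesion. The single-target arm receives active DLPFC with sham M1, and the dual-target arm receives both actively. Localization of stimulation site confirms the fixed side: the DLPFC is found by a method "which involves translating 5 cm forward from the left M1 region".
- **Rationale.** Background and rationale {6a} argues from imbalance between the hemispheres: after a stroke "it is easy to cause a relative increase in excitability of the intact hemisphere".
- **Eligibility.** Eligibility criteria {10} require right-handedness but set no lesion side. On timing they say only that the patient "had mild to moderate cognitive impairment after the stroke".
- **Allocation.** Implementation {16c} describes one ranked list of random numbers, cut into three sets: "Numbers 1–19 are for the control group", with the next two sets of 19 for the single- and dual-target arms. No strata are named.
- **Analysis.** Statistical methods {20a} state that "one-way analysis of variance was used for comparison between multiple groups", followed by LSD-t comparisons, with Kruskal–Wallis for non-normal data. Hemiplegic side appears only among the descriptive items: "count data (such as stroke type, hemiplegic side, and stroke risk factors". Section {20b} adds: "There are no subgroup analyses planned".

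**The concern.** In a left-hemisphere stroke, both dual-target sites lie in the damaged hemisphere. In a right-hemisphere stroke, the DLPFC site lies in the intact hemisphere and the M1 site in the damaged one. The single-target arm changes in the same way, because its one active site is on the damaged side in left strokes and on the intact side in right strokes. Lesion side may also be related to the cognitive scores themselves.

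With 19 patients per arm and no strata, the arms can differ visibly in lesion side by chance. A test with group as its only factor cannot correct for this, although the trial already collects what is needed. At stake are the precision of the arm differences and the ease of defending them if the baseline table shows an imbalance.

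**Working it through.** **The plan's own figures.** The three number ranges in {16c} give 57/3 = 19 per arm. The 20% expansion in {14} agrees with 15 evaluable per arm: 45/0.8 = 56.25, rounded up to 57. The article gives no effect size, SD or power, so every outcome-scale figure below rests on a stated assumption.

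**1. Chance imbalance in lesion side.** Assume that half of the patients have left lesions. With X2 and X3 the left-lesion counts in the single- and dual-target arms, each Bin(19, 0.5), X3 − X2 + 19 is Bin(38, 0.5). Then:

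- P(|X3 − X2| ≥ 4) = 0.256.
- For any of the three pairs of arms, the probability is about 0.49 (simulation).

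Permuting 57 patients into 19/19/19, with left-lesion shares of 40%, 50% and 60%, gives 0.255, 0.260 and 0.250 for the single- versus dual-target pair. A difference of 6 or more has probability 0.07 to 0.08. The result hardly depends on the assumed share.

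**2. Effect of such an imbalance.** Assume that lesion side shifts the MMSE by 2 points. A difference of 4 of 19 moves the arm contrast by 4/19 × 2 = 0.42 points. The standard error of a difference between two arms is SD × √(2/19) = 0.324 × SD.

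**3. Variance explained by side.** With a share of one half, this is 0.5 × 0.5 × 2² / SD² = 1/SD². The equivalent number per arm is 19/(1 − R²).

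| Assumed SD | SE of difference | 0.42 / SE | R² = 1/SD² | Equivalent n per arm |
|---|---|---|---|---|
| 3 | 0.97 | 0.43 | 11% | 21.4 |
| 4 | 1.30 | 0.32 | 6% | 20.3 |
| 5 | 1.62 | 0.26 | 4% | 19.8 |

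On these assumptions, adjusting for side alone is worth between about one and two and a half patients per arm.

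**4. Estimates by side.** At a share of one half, each arm has about 19 × 0.5 = 9.5 patients per side. A two-sided 5% test of one arm against another within one side then has about 59% power even for a standardised difference of 1.0 (normal approximation). With 7.5 evaluable patients per side, power is about 49%. A confirmatory test by side is not realistic.

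**The case against.** Unstratified randomisation with an unadjusted comparison is valid. The standard error already allows for chance imbalance, and the 0.42-point shift is well under half of it. This stands: the matter is precision, not validity. The sizes of effect are assumed, and the gain from side alone may be small. This also stands.

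Some stronger readings are tempting, but the documents do not support them:

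- **That the rationale contradicts the intervention.** The background describes hemispheric imbalance and says that rTMS regulates it. It does not predict a different cognitive benefit by lesion side. The reason given for combining targets, in Strengths, is that cognition and movement promote each other, which does not depend on side.
- **That only the dual-target arm is affected, or that a null average would hide a benefit on one side.** Left DLPFC is active in both active arms. What the dual-target arm adds is M1 in the damaged hemisphere, whatever the side. A dual-versus-single effect that differs by side would need an interaction between the two sites, and nothing in the article shows one.
- **That time since stroke is unrestricted.** The article states no limit, but eligibility rests partly on cited diagnostic guidelines that are not shown. A limit there cannot be excluded, and no size can be given for this factor.
- **That the remaining patients should be allocated within strata.** Recruitment was under way at the time of writing, and the list is fixed at 19/19/19. Changing it mid-trial is a debatable trade-off, and adjustment in the analysis needs no such change.

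The article's brevity is not a full answer, because it names the allocation scheme and the test, and neither uses lesion side.

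**Conclusion.** The point holds as one of precision and of presentation. Lesion side determines which hemisphere is stimulated relative to the lesion in both active arms, and the stated analysis uses side only descriptively. There is about a 26% chance that the single- and dual-target arms differ by 4 or more of 19, for left-lesion shares of 40% to 60%. The consequence depends on how prognostic side is, which the documents do not say. For an assumed 2-point MMSE shift, side explains about 4% to 11% of variance as the SD runs from 5 to 3. The primary comparison also omits the baseline score. No baseline-to-follow-up correlation is given, so that loss is not quantified here. Nothing in this point invalidates the randomisation or inflates the type I error.

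**What to change.** In Statistical methods {20a}, replace the one-way ANOVA for MoCA-BJ and MMSE with an ANCOVA of the post-treatment score on group, baseline score and lesion side, and take the pairwise group differences from that model. Derive lesion side from the recorded hemiplegic side, with a separate category for bilateral or unclassifiable lesions, because the eligibility criteria neither require hemiplegia nor exclude bilateral lesions. Add log time since onset if the medical record holds it. If the dual-minus-single difference is shown by side, present it as descriptive only, with confidence intervals, and say so in {20b}.

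**Cost.** This needs a change of analysis wording and no change to allocation. Baseline score and side use two degrees of freedom, or three if the extra category is occupied. Log time, if added, uses one more. The one-way ANOVA leaves 57 − 3 = 54 residual degrees of freedom (45 − 3 = 42 if 15 per arm are evaluable). Each one spent costs roughly 1/54, about 2%, in precision. If side explains only 4% of variance, about half of its gain is used up. The change should be made before the group comparisons are seen.

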### Objectives {7}

The objectives of this study are:To examine the efficacy of conventional treatment in improving cognitive function in stroke patients;To evaluate the efficacy of single target high-frequency rTMS stimulation in improving cognitive function in stroke patients;Explore whether the therapeutic effect of dual-target rTMS on cognitive function in PSCI patients is better than that of a single target; andAnalyze the mechanism of high-frequency rTMS in improving cognitive impairment after stroke using indicators such as brain Doppler ultrasound and serology.

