### Trial design {8}

This study will include a single-blind, 3-arm, parallel design, randomized superiority controlled trial with a distribution ratio of 1:1:1. Eligible patients will be randomly assigned to the conventional treatment group, single target stimulation group, or dual target stimulation group and will receive intervention treatment for 4 weeks each. This research protocol follows the SPIRIT reporting guidelines [8], as shown in Fig. 1.

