## Interventions

### The explanation for the choice of comparators {6b}

All patients will receive routine rehabilitation treatment (40 min per day, 5 days per week, for 4 weeks), with one-on-one physical and occupational therapy provided by qualified rehabilitation therapists.

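### Objective 1 asks for the efficacy of conventional treatment, but every arm receives it, so only an uncontrolled before-after test is left to answer it

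*Protocol article*

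**What the plan says.** Objectives {7} opens with "To examine the efficacy of conventional treatment in improving cognitive function in stroke patients". Its next two items are the efficacy of single-target rTMS and whether dual-target does better than single-target.

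Trial design {8} sets up three parallel arms, 1:1:1: "Eligible patients will be randomly assigned to the conventional treatment group, single target stimulation group, or dual target stimulation group". The explanation for the choice of comparators {6b} then gives the background therapy to everyone: "All patients will receive routine rehabilitation treatment (40 min per day, 5 days per week, for 4 weeks"). Intervention description {11a} shows that the arm called conventional treatment in {8} also receives sham stimulation at both the left DLPFC and the ipsilesional M1.

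Statistical methods {20a} names two kinds of comparison for normally distributed outcomes. Between arms, "one-way analysis of variance was used for comparison between multiple groups", with LSD-t tests (Kruskal–Wallis if the data are not normal). Within arms, "paired *t*-test was used for patients before and after treatment". The significance level is 0.05 throughout. Outcomes {12} and Participant timeline {13} give two assessments only, W0 and W5.

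**The concern.** Efficacy of a treatment means a difference from what would have happened without it. Here nobody goes without conventional treatment, so randomisation provides no estimate of that difference. What remains for Objective 1 is the change from W0 to W5 inside one arm, tested against zero.

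A change against zero contains everything that moves scores over those weeks, whether or not rehabilitation contributes. If the plan is followed as worded, a significant paired test in the control arm would be the evidence for an efficacy claim that the trial cannot support. A separate analysis plan could not repair this, because no analysis can supply the missing comparator.

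**Working it through.** **1. Which contrasts exist**

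| Arm | Routine rehabilitation | Left DLPFC | Ipsilesional M1 |
|---|---|---|---|
| Group 1 (control) | yes | sham | sham |
| Group 2 (single target) | yes | active | sham |
| Group 3 (dual target) | yes | active | active |

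The rehabilitation column is constant, so it cancels from every between-arm difference. The three available contrasts (2 vs 1, 3 vs 1, 3 vs 2) estimate effects of active stimulation. None estimates the effect of conventional treatment.

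**2. What the paired test estimates in Group 1**

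Mean change = effect of rehabilitation + spontaneous recovery + retest practice + sham response (+ regression to the mean, see step 5). With one arm and two time points these terms cannot be separated.

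**3. Arm size**

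57/3 = 19 per arm. Sample size {14} allows 20% for dropout, and 15/0.8 = 18.75, rounded up to 19, so 15 completers per arm is consistent with the plan. The base figure itself cannot be reproduced, because no difference, SD or power is stated. The point does not depend on it.

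**4. How often the paired test is significant with no specific effect**

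The documents give no non-specific gain and no SD of change, so both are assumed and varied. The test is taken as two-sided at 0.05. For n patients, mean gain g and SD of change s, the t statistic has n − 1 degrees of freedom and noncentrality λ = (g/s)√n. The rejection probability is P(|t| > t_crit).

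- n = 19, t_crit = 2.101: g = 1.5, s = 3 gives λ = 0.5 × 4.359 = 2.18 and probability 0.541. With g = 2, s = 3, λ = 2.91 and probability 0.785.
- n = 15, t_crit = 2.145: the same gains give λ = 1.94 and 2.58, with probabilities 0.438 and 0.671.

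Grid for n = 19:

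| Gain (points) | SD 2 | SD 3 | SD 4 |
|---|---|---|---|
| 0.5 | 0.178 | 0.106 | 0.081 |
| 1 | 0.541 | 0.280 | 0.178 |
| 1.5 | 0.871 | 0.541 | 0.340 |
| 2 | 0.984 | 0.785 | 0.541 |
| 3 | >0.99 | 0.984 | 0.871 |

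With no gain at all the value is 0.05.

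For comparison, 20,000 simulated trials with three arms of 19, a shared gain of 2, SD 3 and no specific effect gave at least one significant paired test in 99% of trials and all three significant in 49%. A one-way ANOVA on the same changes was significant in 4.8%. The between-arm test keeps its level because the shared gain cancels.

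**5. Regression to the mean**

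Eligibility criteria {10} selects patients on the two primary scales, "with a score of 9 < MMSE < 27 and a score of 9 < MoCA < 26". I simulated the MMSE window under assumed values (reliability 0.8, SD 5). If the screening score also serves as baseline, the spurious gain is about 0.14, 0.31 and 0.5 points for source means of 20, 22 and 24. It is about 0 for a source mean of 18, where the lower and upper limits offset each other. If the scale is given afresh at W0, it is about 0 throughout. Participant timeline {13} and Recruitment {15} place baseline evaluation after screening and consent, but do not say whether the screening score is reused.

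**The case against.** The strongest reply is that the trial's real questions are protected. The abstract states the aim as dual-target against single-target and usual care, Trial design {8} calls it a superiority trial, and {20a} plans between-arm tests. On this view Objective 1 is loose wording and the paired tests are a customary supplement. Most of this stands. Objectives 2 and 3 can be answered by the planned comparisons, and nothing in the text makes the paired tests the evidence for them. It does not rescue Objective 1, which is listed as an objective in its own right and has no other analysis.

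A reader might go further and infer that the authors intend to judge dual against single by noting that one arm improved significantly and the other did not. That would be a poor rule: for two arms with identical effects, 2p(1 − p) gives a 0.50 or 0.34 chance of exactly one significant result at p = 0.54 or 0.785. But the protocol does not plan it. It is a misreading to guard against, not an error in the text.

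It is also fair to object that the documents give no figure for recovery, practice or sham response. One can say that scores could rise without a specific effect, not that they will. For the same reason a single narrow range such as 0.54 to 0.79 would give false precision, and regression to the mean enters only if the screening score is reused.

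**Conclusion.** Objective 1 cannot be answered by this design. That conclusion follows from the protocol's own description of the arms and the analysis, and needs no outside figure.

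The size is illustrative. Across the assumed grid, a paired test in an arm of 19 is significant with probability from about 0.08 to over 0.99 when there is no specific effect, against a nominal 0.05. In the middle of the grid (gain 1.5 to 2, SD 3) it is 0.54 to 0.79, or 0.44 to 0.67 with 15 completers. A significant result would therefore say little about the efficacy of conventional treatment.

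The randomised comparisons for Objectives 2 and 3 are untouched. The correction is cheap, and should be made so that the stated objective matches what can be concluded.

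**What to change.** - Reword Objective 1 as: describe the change in cognition in the control arm (routine rehabilitation plus sham rTMS). Naming the sham component matters, because the arm does not show rehabilitation alone.
- In {20a}, label the paired t-tests descriptive and report within-arm changes as a mean with 95% confidence interval.
- State that every efficacy statement rests on the randomised contrasts: single vs control, dual vs control and dual vs single. The dual vs control contrast belongs in the list, because the abstract names usual care as a comparator.

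This needs no extra patients, visits or change to treatment. The trial is registered and was recruiting when the article was written, so the protocol and registry wording would both need updating. What is given up is the option of reporting significant improvement within an arm as a finding.
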